### Data analysis

The data analysis will identify the impact of ‘Intention to treat’ at the level of the individual child. The analysis will compare the change in an outcome measure (at time of data collection minus at baseline) for children in the intervention group with children in the control group. Impact evaluations will be conducted on outcomes measures after the 12, 24 and 36 month data collections as well following the data collection after the commencement of the first year of schooling.

For comparisons between the randomised intervention and control groups from the trial it should be possible to estimate the program impact as the difference in mean outcomes between those groups. For continuous outcome variables this will be the difference in mean changes in the outcome between intervention and control groups. For categorical outcome variables it will be differences in the change in the proportions of children in each category between intervention and control groups. For comparisons between the EYEP intervention group and the control group from LSAC a quasi-experimental matching method (difference-in-difference) will be used. Statistical significance will be established via t-tests for individual outcomes or Hotelling T tests for groups of outcomes.

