### Sample size and power calculations

The sample size has been determined taking into account both the numbers of observations needed to have sufficient power to detect likely effect sizes and the capacity of the CPS childcare centre where EYEP is being implemented. There is no previous Australian study of an intervention similar to EYEP, therefore calculation of the required sample size has been done using impact sizes estimated for the Abecedarian project. Impact sizes from the Abecedarian project are above those for most other early years programs
[21], however, this can be attributed to its being an extensive and long-term intervention. The similar scale of intervention in EYEP makes Abecedarian an appropriate benchmark for this study. We use impact estimates from the Abecedarian project for IQ at 18 months and at 48 months (
[35] page 1918).

The sampsi routine in STATA was used to calculate the necessary sample size. When type one error is set at 0.05 and type two error set at 0.1 (power = 0.9), the minimum required sample size (per group) is 12 children based on the impact on IQ at 18 months IQ and 19 children based on the impact on IQ at 48 months. We then adjust this required sample size in two ways. First, we take into account that our sample will include families with multiple children. Based on the sample from the pilot phase of EYEP we estimate the number of children per family to be 1.35. We assume perfect correlation of outcomes between siblings which therefore requires expanding the minimum sample size by 1.35. Second, we incorporate an estimated attrition rate of 20 per cent per annum for the intervention and control groups (including item non-response). These adjustments result in a minimum sample size per group of 32 children. Hence it is expected that the sample size of 45 children in intervention and control groups will comfortably meet sample size requirements. It also provides a margin of safety in case standard errors in estimates of the impact of EYEP are larger than for the Abecedarian trial. All children in the Abecedarian trial were enrolled prior to reaching 6 months of age, while children recruited into the EYEP trial have been from a broader range of ages, up to 3 years. To the extent that age of enrolment is a source of variability in impact sizes, our estimates of impact size may therefore have larger standard errors than the Abecedarian study.

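### The minimum of 32 per group does not carry 20% annual attrition to 36 months on the larger benchmark; that needs 51, so 45 falls slightly short at that wave

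*Protocol article*

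**What the plan says.** All the figures are in the protocol article, Sample size and power calculations. The error rates are fixed first: "When type one error is set at 0.05 and type two error set at 0.1 (power = 0.9"). Two unadjusted requirements follow, taken from the benchmark trial. The smaller is given as "the minimum required sample size (per group) is 12 children based on the impact on IQ at 18 months IQ". The larger, which uses the later IQ measurement, is put at "19 children based on the impact on IQ at 48 months".

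Two adjustments are then described. The sibling adjustment multiplies by 1.35, the pilot's estimate of children per family, with outcomes of siblings taken as perfectly correlated. The attrition adjustment reads: "Second, we incorporate an estimated attrition rate of 20 per cent per annum for the intervention and control groups (including item non-response"). The result is one number: "These adjustments result in a minimum sample size per group of 32 children". The section concludes: "Hence it is expected that the sample size of 45 children in intervention and control groups will comfortably meet sample size requirements". It adds that 45 also leaves a safety margin in case standard errors exceed those of the benchmark trial.

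The Data analysis section sets the evaluation times: "Impact evaluations will be conducted on outcomes measures after the 12, 24 and 36 month data collections", with a further one after school entry. The Aims and hypotheses section places the expected benefits at the end of the intervention and six months into the first school year. The Intervention and control group section gives the length of participation as three years, or until school entry.

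**The concern.** Attrition is stated as an annual rate, but the evaluations run to 36 months and beyond, so the required enrolment depends on the wave. A single minimum with no wave attached cannot be checked against that design. If 32 rests on one year of attrition, it leaves out the second and third years. If it rests on three years, it uses the less demanding of the plan's two benchmarks.

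What is at stake is the assurance built on 32. A reader is told that 45 per group clears the requirement with room to spare, and that the spare room can absorb larger standard errors, which the section itself thinks possible because children enrol over a wider age range than in the benchmark trial. At 36 months, on the larger benchmark, there is no spare room.

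**Working it through.** **Inputs** (protocol article, Sample size and power calculations): unadjusted n = 12 or 19 per group; sibling factor 1.35; attrition 20% per annum, so a fraction 0.8 is kept each year; 45 enrolled per group; type I error 0.05, taken as two-sided because sidedness is not stated; power 0.90.

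**Formula:** required n per group = unadjusted n × 1.35 / 0.8^years.

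**Reproducing 32**

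- Smaller benchmark, three years: 12 × 1.35 / 0.512 = 31.64, which rounds to 32.
- Larger benchmark, one year: 19 × 1.35 / 0.8 = 32.06, which is 32 if rounded to nearest and 33 if rounded up.

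For the larger benchmark over three years, other ways of applying the attrition do not give 32 either. Multiplying by 1.2³ gives 44.3, and treating the loss as a simple 60% gives 64.1.

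**Larger benchmark at each wave** (19 × 1.35 = 25.65)

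| Wave | Calculation | Minimum per group | Enrolled |
|---|---|---|---|
| 12 months | 25.65 / 0.8 = 32.06 | 33 | 45 |
| 24 months | 25.65 / 0.64 = 40.08 | 41 | 45 |
| 36 months | 25.65 / 0.512 = 50.10 | 51 | 45 |

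**Power of 45 per group.** The benchmark effect sizes are not in the document, so the standardised effect is recovered from n = 19 by the normal approximation: d = √(2 × (1.96 + 1.2816)² / 19) = √(21.01 / 19) = 1.05. With perfect sibling correlation, the number of independent families per group is m = 45 × 0.8^years / 1.35, and power = Φ(d × √(m/2) − 1.96).

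| Wave | Children remaining | Families m | Power, normal | Power, t distribution |
|---|---|---|---|---|
| 12 months | 36.0 | 26.7 | 97% | 96% |
| 24 months | 28.8 | 21.3 | 93% | 92% |
| 36 months | 23.0 | 17.1 | 87% | 85% |

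The t column keeps d = 1.05. If 19 was itself rounded up from just over 18, the normal-approximation power at 36 months is 88%.

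**Two further checks at 36 months**

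- Enrolling only the stated minimum of 32 would leave 32 × 0.512 / 1.35 = 12.1 families and about 74% power, so 32 is not a minimum for 90% power at that wave on this benchmark.
- The annual attrition at which 45 just suffices is 1 − (25.65 / 45)^(1/3) = 0.171, about 17%.

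**The case against.** The best defence is that no arithmetic slip has been shown. If requirements are always rounded up, 32.06 becomes 33, and only the smaller benchmark over three years gives 32. On that reading the authors did compound attrition over the whole intervention, and the issue is only which benchmark governs. The section never assigns the 48-month benchmark to the 36-month wave, and on the 18-month benchmark (d = √(21.01 / 12) = 1.32) 45 per group gives about 97% power at 36 months. This stands as far as it goes: the document does not show which route was taken. It does not rescue the conclusion, because the section presents 19 as one of its two requirements, and the single minimum does not meet that requirement at the last in-programme evaluation.

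The second defence is that the plan is already conservative. Perfect sibling correlation is the worst case. With a simple design effect of 1 + 0.35 × ICC (an assumption that ignores variation in family size), 45 × 0.512 / 1.21 = 19.04 at ICC = 0.6, so 45 would give 90% power at 36 months for an ICC up to about 0.6. Allowing for varying family size weakens this a little, to about 89% at ICC 0.5. The 20% also includes item non-response already. This stands, and it keeps the practical gap small.

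Two stronger readings are tempting and are not supported. A reader might infer that the trial is underpowered throughout, but on the larger benchmark 45 is enough at 12 and 24 months. A reader might also infer that power in school must be lower still. That depends on the time from entry to the school wave, which the document does not fix: children may enrol at any age up to three, and participation may end at school entry before 36 months. At 2.5 years the requirement is 25.65 / 0.8^2.5 = 44.8, which 45 meets. At 3.5 years it is 56.0, so 57, which 45 does not meet.

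**Conclusion.** The concern holds, within limits. The minimum of 32 does not combine the plan's larger benchmark with its own annual attrition to 36 months. That combination needs 51 per group (102 in total) against 45 (90 in total), a gap of six children per group. About 17 independent families per group would remain where 19 are needed, and power is about 87% (about 85% with the t distribution) instead of 90%.

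This is an error in a stated figure and in the assurance drawn from it, rather than a serious loss of power. It rests on attrition of 20% compounding each year, perfect sibling correlation, a two-sided test, and an effect recovered from the rounded 19. The 12 and 19 cannot be checked, because the benchmark effects and standard deviations are not in the document.

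**What to change.** In Sample size and power calculations:

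- State which benchmark and how many years of attrition give 32.
- Give the minimum per group and the power of 45 per group at each wave. On the 48-month benchmark the minimum is 33 at 12 months, 41 at 24 months and 51 at 36 months, with power of about 97%, 93% and 87% (normal approximation).
- Limit the statements that 45 comfortably suffices and leaves a safety margin to the waves where they hold: on this benchmark 12 and 24 months, not 36.
- Say that power at the school wave depends on the time from entry to that wave, and give it under a stated assumption about that time.

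The cost is wording only. No extra children are enrolled and no analysis changes; the figure stated for 36 months becomes less favourable.

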## Discussion

Abuse and neglect of children in their early years introduces long-term barriers to their development and impose substantial costs on a society. Hence the net gains to a society from remedying the consequences of that abuse and neglect are potentially large. EYEP is an innovative early years intervention, seeking as it does to address both the consequences of abuse and neglect on children’s brain development and to redress their learning deficiencies. This is the first RCT of an early years intervention of this intensity and duration that has this dual focus. Furthermore, there is a particular need for empirical evidence about the effects, and the relative costs and benefits, of early years education and care for at-risk children in Australia.

There is a large population of children in Australia for whom the EYEP is relevant. Using national data, it has been estimated that at any time there are 36,000 pre-school children in Australia in the same circumstances as the children eligible to participate in the EYEP trial, requiring casework services on the grounds of risk of child abuse and neglect
[36, 37]. While the benefits of early and sustained education for vulnerable children may be well-established, currently those at-risk children who would benefit most seem least likely to have access to appropriate education and childcare in Australia. A recent report concluded that the Department of Education and Early Childhood Development ‘cannot demonstrate that early childhood services are accessible when and where needed, especially for vulnerable children’
[38]. Hence, the findings from the EYEP trial can influence policy for childcare and education that will affect a large national population.

The importance of having Australian studies of the impact of early childhood programs is that findings from international research cannot automatically be applied to Australia. This is because differences in the cultural context, family risk factors, and the family support service system between Australia and other countries, may affect how the program works. For example, participants in both the Perry and Abecedarian interventions were largely African-American, and lived in small cities (Ypsilanti and Chapel Hill). As well, the most well-known programs enrolled participants a long time ago, in the 1960s and 1970s, and were conducted in small cities. Doing the EYEP study will provide up-to-date evidence that is relevant to the urban environment in Australia.
